#### Data analysis.

Audio recordings of the cognitive interviews will be transcribed and fully de-identified. Several procedures will be followed to ensure rigor and adherence to the cognitive interview procedure and appropriate verbal probing. Each researcher will review results to make decisions on revising, retaining, deleting, or adding items in the PALCARE tool. As recommended by previous literature, we will review each item to examine participants’ understanding and ability to respond to each item. Correlations of the PALCARE and the global readiness will be used to demonstrate convergent validity. Correlations of the two assessments of PALCARE will be used to demonstrate test-retest reliability. In addition, we will compare the scores across pretest and posttest using paired-samples t-tests.

The Question Appraisal System (QAS) [76] will be used to analyze the interview data and identify sources of response bias within and across the PALCARE items. The QAS is a coding tool used to evaluate questions based on prespecified types of problems within categories. The QAS has eight problem categories: a) reading; b) instructions; c) clarity; d) assumptions; e) knowledge/memory; f) sensitivity bias; g) response categories; and h) other. The first QAS category targets researchers and is not applicable to older adults with cancer. Thus, we will examine each PALCARE item for the seven remaining QAS problem categories. Each category has multiple specific problem types that could be identified [75]. Decisions of retaining, revising, or deleting items will depend on its importance or relevance to PC readiness in older adults with cancer, clarity of instructions to complete the survey, difficulty of items etc. The eight problem categories of QAS and their description are listed in Table 3.

**Table 3 pone.0323366.t003:** QAS Overall Categories and Their Description.

QAS Category	Description
1. Reading	Determine if it is difficult for the interviewers to read the question uniformly to all respondents.
2. Instructions	Look for problems with any introductions, instructions, or explanations from the respondent’s point of view.
3. Clarity	Identify problems to communicating the intent or meaning of the question to the respondent.
4. Assumptions	Determine if there are problems with assumptions made or the underlying logic.
5. Knowledge/memory	Check whether respondents are likely to not know or have trouble remembering information.
6. Sensitivity/bias	Assess questions for sensitive nature or wording, and for bias.
7. Response categories	Assess the adequacy of the range of responses to be recorded.
8. Other	Look for problems not identified in Steps 1–7.

Following decisions related to retention, deletion, and revision of items, we will review the new PALCARE tool to ensure its items reflect all eight domains of PC listed in the NCP guidelines and the major dimension of Readiness to Change Framework.

This study is a three-years project. The timeline and study related activities are listed in Table 4.

**Table 4 pone.0323366.t004:** Timeline for Study Related Activities.

Tasks	Pre-award	Year 1/Quarter				Year 2/Quarter				Year 3/Quarter			
		**1**	**2**	**3**	**4**	**1**	**2**	**3**	**4**	**1**	**2**	**3**	**4**
Obtain IRB approval													
Start up													
Hire and train research assistants													
Aim 1: Phase 1 Semi-structured interview; data analysis & initial items for PALCARE tool													
Aim 2: Phase 2 Two rounds of expert panel review and analysis													
Aim 2: Phase 3 Focus group with experts and analysis													
Aim 2: Phase 4 Cognitive interviews with dyads and analysis													
Aim 3: Phase 4 Convergent validity and test-retest reliability													
Disseminate findings and prepare future proposal													
Close out													

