#### Aim 3.

Establish preliminary convergent validity and test-retest reliability of the PALCARE tool: We will assess a) convergent validity of the PALCARE tool by correlating the PALCARE with the global readiness to hear about PC from the Perceptions of Palliative Care Instrument (PPCI) [53], and b) test-retest reliability by assessing readiness for PC using the PALCARE tool during the cognitive interview and 2 weeks afterward.

The three specific aims which will be conducted over 4 phases (see Table 1).

**Table 1 pone.0323366.t001:** Overview of methods/specific aim for each study phase.

Specific Aims	Study phase
1) Develop PALCARE tool	**Phase 1**: Semi-structured interviews with a diverse group of 20 older adults with cancer (White, Black, and Hispanics)
2) Establish the content validity of the PALCARE tool	**Phase 2**: Two rounds of expert panel survey with 10 PC experts; **Phase 3**: Focus group with 6 PC experts **Phase 4**: Cognitive interviews with 20 diverse group of dyads of older adults with cancer and their family caregivers
3) Establish the preliminary convergent validity and test-retest reliability of the PALCARE tool	**Phase 4**: Cognitive interviews with measurement of the global question on PC readiness from the Perceptions of Palliative Care Instrument (PPCI) and repeatedly assessing PALCARE before the cognitive interview and 2 weeks afterward.

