#### Recruitment.

Cognitive interviews will be conducted in 20 older adults with cancer and 20 family caregivers. Participants will be purposively selected to reflect a diversity of cancer types, race/ethnicity (White, Black, Hispanic), and rural versus urban residence. Criteria for family caregivers include a) Being at least 18 years of age; b) Identifying themselves as the family caregiver or being identified as such by the older adult with cancer; c) Ability to communicate in English. Each participant will receive a $50 Amazon gift card as a thank you for completing the survey.

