#### Data collection.

After obtaining informed consent, PALCARE items will be evaluated using cognitive interviewing techniques with a sample of 20 dyads of older adults with cancer and their family caregivers. The substantial sample size of n = 40 for the cognitive interviews will enable us to identify potential problems with the questions and maximally fine-tune the tool [75]. Verbal probing approach of cognitive interviews will be used to solicit the participants’ understanding and interpretation of each item in the PALCARE tool. Verbal probing will allow participants to ask for clarification and comments on wording of each item in the PALCARE tool. We will randomly order the items in the PALCARE tool to ensure the eight PC domains are dispersed throughout the questionnaire [72]. During the cognitive interviewing process, the interviewer will read each question to the participants and ask that they verbalize their understanding of each question. The cognitive interviews will be conducted using a structured interview guide according to the established standard guidelines for cognitive interviewing [74]. According to the guidelines, the cognitive interview will consist of the following process: (a) a PALCARE item will be asked, and the respondent will respond; (b) a series of verbal probes will be asked in reference to that PALCARE item and the respondent’s answer; (c) this process will be repeated for each PALCARE item. Probes will be developed to evaluate several features relevant to item structure and respondent decisional processes according to the verbal probing guidelines provided by Willis, 2005 [74] and will be applied consistently across all PALCARE items. All interviews will be audio recorded.

To help establish preliminary a) convergent validity of the PALCARE tool with the global question on PC readiness from the Perceptions of Palliative Care Instrument (PPCI) [53], and b) test-retest reliability by repeatedly assessing PALCARE before the cognitive interview and 2 weeks afterward, we will ask participants to a) rate their PC readiness using the one question from the PPCI instrument “How ready are you to hear about palliative care today?” (Scoring option, 0 = not at all to 10 = totally); and b) rate their PC readiness using our PALCARE tool before the cognitive interview and 2 weeks after the cognitive interview.

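### Test-retest reliability is to be shown by a correlation plus a paired t-test, and neither measures agreement; an absolute-agreement ICC with its interval would, at almost no cost

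*Protocol article*

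**What the plan says.** The protocol article fixes the analysis in two sentences of the Phase 4 data analysis section. The first is "Correlations of the two assessments of PALCARE will be used to demonstrate test-retest reliability". The second is "In addition, we will compare the scores across pretest and posttest using paired-samples t-tests". No agreement statistic is named anywhere in the article.

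The data come from the cognitive-interview sample: "Cognitive interviews will be conducted in 20 older adults with cancer and 20 family caregivers". The only reason given for its size concerns finding faulty items: "The substantial sample size of n = 40 for the cognitive interviews will enable us to identify potential problems with the questions". No reliability target, precision or power is tied to the retest.

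On timing, the Phase 4 data collection section asks participants to "rate their PC readiness using our PALCARE tool before the cognitive interview and 2 weeks after the cognitive interview", and Table 1 agrees. The Aim 3 statement instead describes "test-retest reliability by assessing readiness for PC using the PALCARE tool during the cognitive interview and 2 weeks afterward". On either wording, all or part of the cognitive interview falls between the two ratings.

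The aim itself is modest: "Establish preliminary convergent validity and test-retest reliability of the PALCARE tool". The Future directions section plans further quantitative psychometric studies.

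**The concern.** Test-retest reliability asks whether the same person gets the same score twice. A correlation asks something else: whether the two sets of scores lie near some straight line. If every respondent scores half an SD higher the second time, or if the scores stretch, the correlation does not move.

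The paired t-test covers part of this gap, because it responds to a shift in the mean. But it gives no index of individual agreement, and with few pairs a non-significant result is weak evidence that nothing shifted.

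A shift is plausible in this design. Between the ratings, every item is read out, probed and clarified with the respondent, and the article itself lists lack of knowledge about palliative care as a barrier. Readiness scores could move in one direction for that reason alone.

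Agreement matters because the intended use is individual: the abstract and Discussion foresee identifying which patients are ready and acting on that. The coefficient reported here would also inform the next psychometric study.

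**Working it through.** **Inputs from the article.** Pairs: 20 if only patients are analysed, 40 if all participants are; the article does not say which. Statistics: a correlation and a paired t-test. The article has no power or precision figure for the retest, so there is none to reproduce.

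**Assumptions not in the article.** Normal scores, equal SDs at both ratings, two-sided 5% level, true correlation ρ of 0.70 or 0.80, shift *d* in SD units. The rows for 40 pairs treat all pairs as independent, which is optimistic for members of the same dyad.

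**Step 1: effect of a shift on agreement.** The correlation stays at ρ for any constant *d*. The absolute-agreement, single-measure ICC is ρ / (1 + d²/2). For ρ = 0.80 and d = 0.5 this is 0.80 / 1.125 = 0.71. For d = 0.3 it is 0.80 / 1.045 = 0.77. For ρ = 0.70 and d = 0.4 it is 0.70 / 1.08 = 0.65.

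**Step 2: chance that the t-test detects the shift.** The SD of the difference is √(2(1 − ρ)): 0.632 at ρ = 0.80 and 0.775 at ρ = 0.70. The standardised shift is d divided by this, and power comes from the noncentral t distribution.

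| ρ (= r) | Shift (SD) | ICC | Power, 20 pairs | Power, 40 pairs |
|---|---|---|---|---|
| 0.80 | 0.2 | 0.78 | 27% | 50% |
| 0.80 | 0.3 | 0.77 | 52% | 83% |
| 0.80 | 0.5 | 0.71 | 92% | >99% |
| 0.80 | 0.8 | 0.61 | >99% | >99% |
| 0.70 | 0.3 | 0.67 | 38% | 67% |
| 0.70 | 0.4 | 0.65 | 59% | 89% |
| 0.70 | 0.5 | 0.62 | 78% | 98% |

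So shifts that lower the ICC a lot are usually detected, and those usually missed lower it by a few hundredths. In between, at ρ = 0.70 with 20 pairs, a shift that takes the ICC to 0.65 is missed about four times in ten.

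**Step 3: what a non-significant t-test shows.** The 95% CI for the mean difference has half-width t(0.975, 19) / √20 = 2.093 / 4.472 = 0.47 SDs of the difference. At ρ = 0.80 that is 0.47 × 0.632 = 0.30 score SDs. An observed difference of zero would still be compatible with a shift of 0.3 SD either way.

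**Step 4: precision of the correlation.** Fisher's z for r = 0.80 is 1.099.
- 20 pairs: half-width 1.96 / √17 = 0.475, giving a 95% CI of 0.55 to 0.92.
- 40 pairs: half-width 1.96 / √37 = 0.322, giving 0.65 to 0.89.

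An ICC does not remove this imprecision. An observed consistency ICC of 0.80 with 20 pairs has an approximate 95% CI of 0.56 to 0.92.

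**The case against.** The strongest reply is that the two analyses complement each other. The correlation falls when individuals disagree at random, the t-test responds to a mean shift, and nothing in the article says that a non-significant t-test will be taken as proof of agreement. Much of this stands. A reader might infer that an unreliable tool would readily be declared reliable because a large shift can slip past both checks. The figures do not support that: at ρ = 0.80 with 20 pairs, shifts of 0.5 and 0.8 SD are detected with 92% and over 99% power. Nor does the article state a pass criterion, so any false-pass rate would depend on one supplied from outside.

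Other points against also carry weight:
- The number of pairs may be 40 rather than 20, which improves detection of a shift but does not turn either statistic into a measure of agreement.
- The coefficient is not named, so an intraclass form is not excluded. However, the sentence before uses the same word for PALCARE against a single 0-to-10 question, where an ordinary correlation is meant.
- The absence of a stated confidence interval is, taken alone, ordinary condensation in an article and not a fault.
- The aim is preliminary, further studies follow, and clinical use is made conditional on established reliability and validity.
- A mean shift after the interview may be real change. An absolute-agreement ICC alone would count it as unreliability.

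The last point shapes the fix. None of them makes a correlation or a t-test a measure of agreement.

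**Conclusion.** The point holds in a moderate form. On the natural reading, the stated statistics do not measure what they are meant to demonstrate. The practical loss is limited mainly to small and moderate shifts: about 0.3 SD at reliability 0.80 (52% power with 20 pairs, 83% with 40), and about 0.4 SD at reliability 0.70 (59% with 20 pairs, 89% with 40). The wording also claims more than the sample can give, since an observed r of 0.80 is compatible with a true value as low as 0.55 with 20 pairs or 0.65 with 40. These figures rest on normal scores, equal SDs and the assumed reliabilities, because the article states none. It is a worthwhile, cheap improvement to a preliminary aim. It does not invalidate the study, and the documents do not support treating it as a correction that must be made before the study proceeds.

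**What to change.** Replace the two sentences in the Phase 4 data analysis section with wording to this effect:

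> Test-retest reliability will be estimated by the two-way, absolute-agreement, single-measure ICC with its 95% CI. The standard error of measurement, the mean difference with its 95% CI, and the limits of agreement will also be reported. The consistency ICC or the correlation will be given alongside, so that a mean shift after the cognitive interview can be told apart from random disagreement. Patients and caregivers will be analysed separately. No conclusion about reliability will rest on a t-test p-value.

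The verb should be *estimate*, not *demonstrate*. The timing of the first rating should be made the same in Aim 3 as in Table 1 and the Phase 4 data collection section.

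The cost is a little more analysis on the same paired scores, with no new participants or visits. The headline coefficient may come out slightly lower than an ordinary correlation, and the interval will remain wide.

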## Discussion

Informed by the NCP project guidelines, readiness to change framework, and principles of community-engaged research, this 3-year R15 research study will iteratively develop and establish the content validity, preliminary convergent validity, and test-retest reliability of a palliative care readiness tool for older adults with cancer. To our knowledge the PALCARE would be the first standardized tool to assess readiness for early PC in older adults with cancer. Once the reliability and validity of the PALCARE tool has been established, it can be used clinically by the primary oncology team to assess readiness for PC and refer older adults with cancer to appropriate PC services. The utility of this tool is threefold: a) assess readiness for early PC in older adults with cancer, b) provide/deliver targeted PC that is congruent with their readiness level in the domains where they feel ready, and c) design tailored interventions to inform, educate, and support those who are reluctant or less ready to consider PC in general or do not feel ready yet in certain domains of PC. Over time, this may help facilitate readiness to accept early PC referral and ultimately positive health outcomes and improved quality of life. This is especially important for older adults with cancer who have lower early PC use, including those who belong to racial minority groups, low socio-economic status, or reside in rural under-resourced areas. This tool could also influence tele-PC interventions aimed at underrepresented patients in rural or under-resourced areas. Future applications can be expanded to all adult oncology patients, family caregivers, and other seriously ill populations. Consistent with the goal of an R15 study, additional impact of this project includes planned activities to enhance the university’s research environment by providing opportunities for students with limited to no prior interdisciplinary clinical research experience with rich research opportunities.

## Future directions

After completing this study and developing the PALCARE tool, our next step is to establish the psychometric validity and reliability of the PALCARE tool by conducting quantitative studies. After we establish the validities and reliabilities of the PALCARE tool, our longer-term goal will be to conduct a randomized controlled trial to examine if the use of a PALCARE tool will result in early PC referral and utilization among older adults with cancer leading to an improved QoL.

## Dissemination plans

Study results will be disseminated using multiple platforms included but not limited to a) peer-reviewed journal article publications in multiple leading journals such as *Journal of Geriatric Oncology, Journal of Hospice and Palliative Nursing, Journal of Palliative Medicine, American Journal of Hospice and Palliative Medicine* b) presentations at annual conferences of several national and international geriatric, palliative care, oncology, and nursing professional organizations such as the Gerontological Society of America (GSA), International Society of Geriatric Oncology (SIOG), Hospice and Palliative Nurses Association, American Academy of Hospice and Palliative Medicine (AAHPM), Southern Nursing Research Society (SNRS) c) social media platforms such Blue Sky, Twitter, and LinkedIn, and d) community engagement activities such as clinical site events, stakeholder meetings or community forums.

Once the results have been disseminated via publications and conference presentations, the de-identified data sets will be made available to interested researchers. Public use and restricted access study data and associated documentation will be made available to the research community free of charge through the deposit at National Archive of Computerized Data on Aging (NACDA).

## Conclusion

In conclusion, this 3-year research project will iteratively develop and validate a palliative care readiness tool which is critically essential for older adults with cancer who have high symptom burden and unmet needs but are highly likely to underutilize palliative care. Our PALCARE tool has great potential to reduce existing disparities and promote equitable access and utilization of palliative care among older adults with cancer.
